##### Sample Size and Sampling

At baseline, clustered and random sampling will be applied. University students will be enrolled consecutively from randomly selected classes (clusters) at the UCM and UniLicungo. Considering that the baseline survey will serve as identification and enrolment point of participants to the cohort, and the main purpose is to look for differences on determinants and behavior changes between groups (students exposed to the full program and those not exposed); based on a 95% confidence interval, desired confidence interval half-width of 0.15 and Cohen's d of 0.2, a total of 687 participants are needed (32). Assuming a 20% dropout, the final sample size is 824. Hence, the goal is to include 412 participants per university. At each university, ten classes (graduation programs) will be randomly selected, and study participants will be enrolled from selected classes until the sample size is completed starting from the first class randomly identified.

Inclusion criteria

First year university students studying at one of the two universities in faculties located in Beira city.Being aged 16–25 years old.Having residency in Beira city for the entire academic year.

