The health advisor will offer services according to the national guideline (17). He/she will also record the results of STI/HIV screening in the specific form with participant identification number (code). A standard operation procedure (SOP) will be provided to the health advisors. The health advisors will fill in a checklist for each client assisted, they will also be asked to fill in the client record sheet with required data from all clients regardless of being a study participant.

All quantitative data will be processed and analyzed using SPSS (Statistical package for Social Sciences, V. 25), descriptive statistics and proportions will be reported. The baseline data will be compared using t- tests and Chi-square tests. After intervention, data from different universities will be compared using multilevel regression models considering the baseline values and nesting of students within classes. Multilevel regression model analysis has been referred to be an eligible method to analyze data from research with a hierarchical structure, and variables measured at different levels and time-points (35–38). This method enables an assessment of the effects of variables measured at different levels of the hierarchy, for example class, student and repeated points of measure indeed, many benefits has been mentioned (36). The data from the baseline survey will be used to estimate the effect size. Additionally, Cohen's d test will be used to estimate the effect size with 95% confidence interval, relative risk and Odds ratio will be determined to measure the extent to which the intervention affects the (determinants of) behavior.

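### The multilevel comparison is sound, but three statements beside it need correcting: an effect size taken from baseline data, student-level baseline tests, and d, RR and OR not tied to the model

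*Protocol article*

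**What the plan says.** All the statements at issue stand in the closing analysis paragraph of Effect Evaluation, Study Procedure, in the Protocol article. In order:

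- Baseline: "The baseline data will be compared using t- tests and Chi-square tests".
- After the intervention, the two universities are "compared using multilevel regression models considering the baseline values and nesting of students within classes".
- Then: "The data from the baseline survey will be used to estimate the effect size".
- Then: "Additionally, Cohen's d test will be used to estimate the effect size with 95% confidence interval, relative risk and Odds ratio will be determined". The stated purpose of these measures is to show how far the intervention affects behaviour and its determinants.

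The section Sample Size and Sampling says that ten classes are drawn at random at each university and that students are enrolled from those classes. It sizes the study on the precision of d: "based on a 95% confidence interval, desired confidence interval half-width of 0.15 and Cohen's d of 0.2, a total of 687 participants are needed". It continues: "Assuming a 20% dropout, the final sample size is 824", and "the goal is to include 412 participants per university".

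**The concern.** Baseline is time 0, at enrolment. The article calls the comparison university a non-equivalent control and lists selection bias among its limitations. A difference at that point describes how the two student bodies differ before follow-up, so an effect size computed from it would be a selection difference under the wrong name.

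The t-tests and chi-square tests assume independent students. If students in the same class resemble each other, baseline p-values are too small and imbalance is declared too often.

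The third statement is less certain. Cohen's d, RR and OR come after the model, introduced as an addition and, for d, as a test of its own. Nothing says they are model outputs. By their usual formulas they would carry any baseline imbalance and have intervals that ignore class. This matters because d is the measure on which the study was sized, and the Discussion expects the findings to inform decisions on expanding the programme.

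**Working it through.** **Inputs from Sample Size and Sampling.** d = 0.2; 95% interval half-width 0.15; total 687; 20% dropout; 824 enrolled; 412 and 10 classes per university. The article gives no intraclass correlation (ICC). The values 0.01, 0.02 and 0.05 are assumptions, as are equal class sizes and use of all 20 classes.

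**Step 1: reproduce the plan's figure.** For equal arms of n independent students, var(d) = 2/n + d²/(4n). Setting 1.96 × √var(d) = 0.15 gives

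n = (2 + 0.2²/4) × (1.96/0.15)² = 2.01 × 170.7 = 343.2 per arm, so 686.3 in total, rounded up to 687.

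Then 687 × 1.2 = 824.4, i.e. 824, or 412 per university. The 687 is therefore the independent-student result with no allowance for class. The only interval for d that the article quantifies is the student-level one.

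**Step 2: design effect.** Students per class: 824/20 = 41.2. DE = 1 + (41.2 − 1) × ICC. A student-level standard error is too small by √DE. The true type I error of a nominal 5% student-level test is 2 × [1 − Φ(1.96/√DE)].

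| Assumed ICC | DE | √DE | Type I error | Coverage of a naive 95% CI |
|---|---|---|---|---|
| 0.01 | 1.40 | 1.18 | 9.8% | 90% |
| 0.02 | 1.80 | 1.34 | 14.4% | 86% |
| 0.05 | 3.01 | 1.73 | 25.9% | 74% |

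The type I error column applies to the baseline tests.

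**Step 3: what this means for d, if it is computed outside the model.** At 824 the naive half-width is 1.96 × √(2.01/412) = 0.137. Multiplied by √DE it becomes 0.162, 0.184 and 0.238. With 687 completers (34.35 per class) the factors are 1.15, 1.29 and 1.63, and the half-width of 0.150 becomes 0.173, 0.194 and 0.245.

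**Step 4: missing baseline adjustment, under the same condition.** Suppose, for illustration only, a time-0 imbalance of 0.1 SD on a stable outcome. It passes almost in full into an unadjusted post-intervention d, which is 0.1/0.2 = half of the planning value.

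**Step 5: what the baseline sentence could mean.** It is not a planning input, since Sample Size and Sampling already fixes d at 0.2. The sentence after it uses the same term, effect size, for the extent to which the intervention changes outcomes. Baseline data can properly supply the SD that standardises d and the values that adjust it, but the sentence does not say this.

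**The case against.** The strongest reply is that the analysis that compares the universities after the intervention already handles both clustering and baseline values. This stands. A reader might infer that the whole effect analysis ignores class, or that t-tests and chi-square tests will judge the programme. The text supports neither: those tests are confined to baseline, and no decision is said to depend on them.

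It can also be said that the article never calls d, RR and OR crude. An odds ratio is the ordinary output of a multilevel logistic model, d can be a standardised model coefficient, and a condensed article may leave such derivations to an analysis plan that is not shown. This stands too, so the third statement can only be put conditionally. A reader might go further and expect a crude d as the headline result, or two conflicting answers for each outcome. The article does not say so, and sizing a study on d does not make a crude d its main analysis. What remains is that the measures are set apart from the model and that the planned precision of d reproduces only with independent students. Together these make the student-level reading plausible.

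Finally, the baseline sentence has a benign reading: baseline data supply the SD or the adjustment. That may be what was meant, but it is not what is written. Nor does the article say that a time-0 difference will be presented as the programme effect, so the fault lies in a rule that would mislead if followed, not in a result certain to be reported.

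**Conclusion.** The point holds in a limited form, and the main post-intervention model is not in question.

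1. The baseline effect-size sentence is wrong as written, whatever the ICC.
2. The baseline t-tests and chi-square tests ignore the sampling unit. Their type I error is about 10%, 14% or 26% at ICC 0.01, 0.02 or 0.05.
3. If d, RR and OR are computed at student level outside the model, they lack baseline adjustment and their intervals are too narrow by about 1.18, 1.34 or 1.73 at the same ICCs. If they come from the model, this part falls away once the text says so.

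The sizes rest on assumed ICCs and on 20 equal classes of about 41. Because classes are filled in sequence until the target is met, fewer classes may be used; classes would then be larger and so would the factors. The corrections should be made, but they concern wording and reporting, not the design.

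**What to change.** - Delete the baseline effect-size sentence, or restate it so that baseline data supply only the standardising SD and the adjustment.
- Describe baseline with standardised differences between the universities, or with comparisons that account for class.
- State that every reported effect measure is derived from the post-baseline multilevel models: d as the baseline-adjusted difference divided by the pooled baseline SD, with the model's confidence interval; OR from the multilevel logistic model; RR from the same model, for example by marginal standardisation.

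The cost is a few sentences and slightly more analysis work. No new data are needed. The intervals will be wider than the student-level formulas would give.

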## Discussion

Evaluation of health promotion programs is seen as an important step in intervention development, because it enables to learn about the effects of interventions and how they are established (22), indeed it opens up the “black box” of the intervention (39). In this study, a combination of process and effect evaluation is proposed. This is a useful and fruitful procedure, since concurrent process evaluation can allow researchers to better interpret findings and understand how the intervention might replicate in similar contexts. Nevertheless, the method can limit biases in estimating effects, while building a detailed comprehension of causality (22) through correlation of process indicators with outcomes (40) to support stakeholders and scientific audience in interpreting the reports.

The result of this study will inform and guide the development of optimal sexual and reproductive health behavior promotion programs targeting university students, using a systematic approach. Having assessed the natural conditions under which intervention targeting STI/HIV prevention issues among university students works, the findings will support public health decision makers to expand the program to other universities (if deemed appropriate) and make adaptions (where needed).

There are many approaches that can be applied to develop, implement and evaluate health promotion interventions, from the narrow one to the most comprehensive such as the Behavior Change Wheel and Intervention Mapping. O'Cathain end colleagues describe eight categories: 1. Partnership approaches; 2. Target population-centered; 3. Theory and evidence-based, 4. Implementation-based, 5. Efficacy based; 6. Stepped based; 7. Intervention-specific and 8. Combination (41). Our study belongs to category 3.

We decided to follow the IM since it is a theory-and evidence-based, systematic and detailed guide regarding what to do, especially on how to perform specific needed activities to achieve intervention transparency (39, 41, 42). Although the approach is time and resource consuming, it is a helpful method which enables the researchers to receive systematized support, while planning and concretizing aims including the whole intervention, from all stakeholders (43, 44).

The program described in this manuscript, which we aim to evaluate, is already in its full implementation, meaning that it might be an unjustifiable and unfeasible procedure to apply a full experimental study design with random allocation to intervention and control group, which would imply excluding some classes or students from the intervention at UCM, while they share the same environment and policies. Hence to have a comparison group, similar in age and level of education, a quasi-experimental design assigning students from another university as comparison group is a rational and acceptable approach to evaluate the effect of the intervention aiming to change (determinants of) behavior with limited biases.

Traditionally, randomized controlled trials have been seen as gold standard for generating casual evidence in health sciences field, especially when it comes to warrant inclusion criteria in systematic reviews and meta-analysis (45, 46). However, for this study, a quasi-experimental non-equivalent control group design was chosen, since the design combines some of the advantages of the full experimental designs with those of no experimental studies, offering distinct advantages compared to randomized controlled trials. Particularly, the design limits some of the threats to external validity that can be seen as a weakness of the full experimental designs (45).

Although quasi-experimental studies have some advantages compared to other designs, it is recognized that they will only result in acceptable or valid inferences when conducted in a way that meet certain assumptions (45). They are recommended when the study pretends to evaluate complex interventions for instance health behavior change (46–48), which is our case. The design will enable to generate outcomes with high external validity since the data will be collected under natural conditions. Admittedly, quasi-experimental study designs as described above, are challenged by some limitations such as lack of individual participant randomization to each arm and need for advanced statistical analysis. The results from this study can be influenced by several pitfalls for instance, selection bias, maturation bias, Hawthorne effect (observation effect), historical bias, regression to mean, ascertainment bias and reporting bias (49–51). Most of these biases will be controlled by using the control group pre-post approach.

## Ethics Statement

The studies involving human participants were reviewed and approved by Interinstitutional Committee on Bioethics of Health - CIBS Sofala. IRB00002657. Written informed consent to participate in this study was provided by the participants' legal guardian/next of kin.

## Abbreviations

AIDS: Acquired Immunodeficiency Virus
BO: Behavior outcome
CDC: Center for Disease Control
CIBS: Comité Interstitucional de Bioética de Sofala
CO: Change Objective
DNAM: Direcção Nacional de Assistência Médica
HIV: Human Immunodeficiency Virus
IM: Intervention Mapping
MISAU: Ministério da Saúde
[name]: [name]
PO: Performance objectives
RK: [name]
RPR: Rapid Plasma Reagin
SOP: Standard Operation Procedures
STI: Sexually Transmited Infection
UCM: Universidade Católica de Moçambique
UM: Maastricht University
UniLlicungo: Unversidade Licungo.
